**Methods/design:**

The efficacy of the SIGMA mHealth intervention will be investigated within a randomized, placebo-controlled trial. The intervention will be set to last 2 months with a 3-month follow-up. Selected participants will be young overweight adults with non-clinical maladaptive eating habits embodied by food cravings, binge eating, and emotional eating. The primary outcomes will be represented by changes in (1) self-reported maladaptive thoughts related to eating and body weight, (2) self-reported maladaptive eating behaviors in the range of urgent food cravings, emotional eating or binge eating, (3) as well as biased attentional processing of food items as indexed by reaction times. Secondary outcomes will be represented by changes in weight, Body Mass Index, general mood, and physical activity as indexed by the number of steps per day.

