#### Sample size

In order to detect a medium effect size (i.e., Cohen’s *d* = 0.50), with a *p* ≤ 0.05 and 80% power, we would need a total of 74 participants, 37 participants per arm (calculated using G*Power, [48]). Assuming that up to 40% of participants will drop out of the intervention [16], a total of 104 participants will be needed (52 participants per trial arm) in order to detect the aforementioned effect size. The 40% percentage dropout rate represents the worst-case scenario as a high dropout rate can be sometimes expected in mHealth or eHealth studies [16].

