### Pre, post, and follow-up evaluation of the primary and secondary outcomes

#### Primary outcomes

Maladaptive thoughts related to eating and body weight will be assessed at T1, T2, and T3 via the Eating Disorders Beliefs Questionnaire (EDBQ; [50]). The 32-item EDBQ consists of four subscales: (1) negative self-beliefs, (2) weight and shape as a means to acceptance by others, (3) weight and shape as a means to self-acceptance, and (4) control over eating. The instrument has good reliability with a Cronbach’s alpha of 0.93, 0.94, 0.88, and 0.86, for the mentioned subscales, respectively, and good construct validity.

Eating behaviors will be assessed via the Dutch Eating Behavior Questionnaire (DEBQ; [51]). The DEBQ has 33 items clustered in three subscales: (1) restrained eating, (2) emotional eating, and (3) external eating. The subscales of the DEBQ have a high internal consistency and factorial validity with a Cronbach’s alpha of 0.95, 0.94, and 0.80 for the restrained, emotional, and external eating subscales, respectively.

Food cravings will be evaluated via the Trait and State Food Cravings Questionnaires (FCS-S, FCS-T; [52]). The FCS has good psychometric properties and assesses constructs as follows: desire to eat, anticipation of positive reinforcement, anticipation of relief from negative states and post-eating mood, lack of control over eating and craving as a physiological state. The FCS-S consists of 15 items, while the FCS-T consists of 39 items. Both questionnaires have good psychometric properties (Cronbach’s alpha of 0.97 for the FCS-T and 0.94 for the FCS-S).

The Binge Eating Scale (BES; [53]) will be used in order to assess the presence of binge-eating behaviors. The BES consists of 16 items, describing behaviors, emotions, and cognitions surrounding a binge episode (e.g., guilt, fear of not being able to stop eating). The BES was demonstrated to have an excellent internal consistency (Cronbach’s alpha of 0.87; [54]).

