### Data analysis

To test the efficacy of the SIGMA intervention against the attention placebo control group a 2 (group: SIGMA intervention group versus attention placebo group) × 3 (time: pre vs. post vs. follow-up) general linear mixed model will be used with regard to the primary and secondary outcomes. Separate analyses will be performed for the “intent-to-treat” and the completer sample. The intent-to-treat principle will be employed [58] with the last observation carried forward method. The Bonferroni-Holm correction will be used to adjust for multiple comparisons. Overall, with a sample of at least 74 participants, the trial will be powered to identify at least a medium effect size (i.e., Cohen’s *d* = 0.50).

App usage data and user activity will be inspected by contrasting; for example, the participants’ self-reported activity with their actual app usage as recorded in the database. This will inform us about any impediments to user adherence, as well as particular usage patterns.

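### The 80% power is claimed at an unadjusted 0.05, but a Holm correction across the six or more primary scores leaves about 57% or less for a single affected outcome

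*Protocol article*

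**What the plan says.** All references are to the protocol article.

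- **Sample size.** The target is d = 0.50 "with a *p* ≤ 0.05 and 80% power", and the result is that "we would need a total of 74 participants, 37 participants per arm". No adjusted significance level appears, and sidedness is not given.
- **Primary outcomes.** Five instruments or tasks are listed and give six scores: EDBQ, DEBQ, the state and trait food-craving questionnaires (FCS-S and FCS-T), BES and a dot-probe attentional bias score. Subscales are described for two of them; for example, "The 32-item EDBQ consists of four subscales", and the DEBQ has three. The abstract groups the primary outcomes into three domains. No lead outcome or composite is named.
- **Data analysis.** A group-by-time mixed model is applied to primary and secondary outcomes, and "The Bonferroni-Holm correction will be used to adjust for multiple comparisons". The next sentence says again that 74 participants power the trial for d = 0.50, without reference to the correction.

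**The concern.** The sample size and the analysis describe different tests. The sample size is for one comparison at 0.05. The analysis applies a multiplicity correction to a trial with six or more primary scores. If the correction spans those scores, the first one declared significant must meet 0.05 divided by their number, and the 80% no longer describes any single primary outcome. If the correction works only inside each outcome, the 80% can stand, but the chance of a false positive somewhere among the primary outcomes is well above 5%.

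The protocol's working hypothesis is one broad statement about maladaptive behaviours and cognitive styles. Readers will take the 80% as the chance of detecting a medium effect on a given primary outcome, and will take the Holm sentence as error control over that statement. With 74 evaluable participants, the plan does not give both in that sense.

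**Working it through.** **Inputs.** From Sample size: d = 0.50, significance level 0.05, power 80%, 37 evaluable per arm, 52 per arm recruited. From Primary outcomes: K scores.

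- By instrument: EDBQ 1 + DEBQ 1 + FCS 2 + BES 1 + dot-probe 1 = 6.
- By subscale: 4 + 3 + 2 + 1 + 1 = 11.
- By abstract domain: 3.

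Assumed: two-sided tests, and equal correlation between outcomes wherever a correlation is needed.

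**Step 1: the plan's own figure.** A two-sided, two-sample t-test at d = 0.50 needs 64 per arm (128 in total) for 80% power. A one-sided test needs 51 per arm (102). At 37 per arm, power is 56.4% two-sided or 68.6% one-sided. The 74 appears only with inputs that are not stated, such as a three-time-point between-group test with correlation about 0.35, or baseline adjustment with correlation about 0.65. This is a separate fault. To isolate multiplicity, the next steps grant the protocol its 80% at 0.05.

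**Step 2: Holm across the primary outcomes, one outcome affected.** Granting 80% at 0.05 fixes the expected test statistic at 1.960 + 0.842 = 2.802. Power at the first Holm step is Φ(2.802 − z), where z is the two-sided critical value at 0.05/K.

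| K | First-step level | z | Power |
|---|---|---|---|
| 3 | 0.0167 | 2.394 | Φ(0.408) = 65.8% |
| 6 | 0.0083 | 2.638 | Φ(0.163) = 56.5% |
| 11 | 0.0045 | 2.838 | Φ(−0.036) = 48.6% |

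**Step 3: Holm across the primary outcomes, every effect truly 0.50.** Later Holm steps are more lenient, so the first step is the worst case. Simulation from the same base, with correlation 0 to 0.8, gives:

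- average per-outcome power of about 66–68% (six) or 58–60% (eleven);
- for six outcomes, at least one Holm rejection in about 99% (correlation 0), 90% (0.5) or 78% (0.8);
- for six outcomes, all six rejected in about 22% (correlation 0) to 56% (0.8).

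**Step 4: Holm only within each outcome.** If each outcome carries a 5% error, family-wise error under independence is 1 − 0.95^K:

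- K = 6: 1 − 0.95^6 = 26.5%;
- K = 11: 1 − 0.95^11 = 43.1%.

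By simulation, correlation 0.5 gives 20.7% and 30.4%, and correlation 0.8 gives 13.9% and 18.0%.

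**Step 5: what 80% at the first step would need.** Sample size scales by ((z + 0.842)/2.802)², which is 1.543 for six and 1.725 for eleven. Applied to the protocol's own 74, this gives 74 × 1.543 ≈ 115 and 74 × 1.725 ≈ 128 evaluable. By plain two-sided t-test it is 99 or 111 per arm.

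**The case against.** Four points on the other side deserve an answer.

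1. **Power can be read as the chance of at least one success.** A reader might infer from the mismatch that the stated power and the error control can never both hold. The documents do not support that. If all six effects are 0.50 and the 80% base is granted, at-least-one power under Holm is 78–99%. This stands, and it limits the point to per-outcome power. However, the protocol never defines power as at-least-one; it gives one effect size, one level and one figure.

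2. **The shortfall could be made to look larger.** A plain t-test at 37 per arm gives first-step power of 29.5% (six) or 22.8% (eleven), and a reader might take these as the cost of multiplicity. They also contain the separate fault that 37 per arm gives only 56% at 0.05. They also rest on a t-test, whereas the plan names a mixed model. The figures in Step 2 start from the granted 80% and do not depend on which model produced it.

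3. **Eleven is an inference.** The article describes subscales as features of the instruments and does not say that each is tested as primary. This stands, so eleven is an upper count. Even three domains give 65.8%, and no rule is stated that reduces the scales to three scores.

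4. **A condensed article leaves detail to other documents.** A reader might treat the undefined Holm family and the missing rule for a positive trial as defects in themselves. They may be settled in a full protocol or SAP that is not shown, so they are not the charge here. The charge is the printed power figure: no Holm family that spans the listed scores gives 80% per outcome at 74.

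**Conclusion.** The point holds for power per primary outcome. With the protocol's 80% at 0.05 granted and Holm applied across the primary scores, power for a single affected outcome is about 57% (six) or 49% (eleven), and 66% if only three domains count. It stays below 80% on average even when every effect is real. Applying Holm only within outcomes avoids that loss but leaves a family-wise error of about 14–27% (six) or 18–43% (eleven).

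These results assume two-sided tests, a normal approximation and equal correlations from 0.8 to 0; the documents give no correlation. That 74 does not reproduce under a plain t-test is a separate matter and would make the shortfall worse.

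**What to change.** - In Data analysis, state that Holm spans the primary outcomes, and list the scores and the time point that form the family. Which scores stay in, and whether the three-month follow-up is included, is the sponsor's choice.
- In Sample size and in the closing power sentence of Data analysis, restate power for that family in one of two ways. Either give per-outcome power at the first-step Holm level, or give at-least-one power with the assumed correlation and effects. The second is suitable only if the claim is limited to the construct whose outcome is significant.

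The cost is a few sentences and a less favourable power figure. Keeping 80% per outcome would instead need a larger sample or a smaller primary family.

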### Ethics

The current trial protocol was approved by the Ethics Committee of the Babeș-Bolyai University and the University of Bucharest. Several measures will be taken in order to protect the participants’ wellbeing and identity as follows.

Firstly, according to the exclusion criteria, participants suffering from psychiatric conditions (i.e., including clinical eating disorders), as well as other serious health conditions that are incompatible with undertaking a weight-loss regimen, will not be considered for inclusion and will immediately be referred to healthcare professionals.

Secondly, if participants’ physical or emotional condition deteriorates during the trial, they will immediately be excluded from the trial and will similarly be referred to appropriate practitioners. Participants will be informed that participation is voluntary and that they may discontinue the intervention at their free will. Any adverse events and other unintended effects of trial interventions or trial conduct will be addressed by the project coordinator ([name]).

With respect to data protection, in addition to user authentication via username and password, all data protection issues will be covered by (1) having the locally stored data written in binary files that are difficult to alter, (2) by ensuring a secure HTTPS data transfer protocol, (3) by having a server authentication of the researchers, and (4) by using user aliases accessed by authorized personnel only. Furthermore, the customized feedback reports of each participant will only be available to themselves and protected by means of unique usernames and passwords.

## Discussion

The SIGMA study is a randomized, placebo-controlled trial entailed to test the efficacy of the SIGMA mHealth intervention against an attention placebo control group. The SIGMA mHealth intervention combines a portable, serious game interface with evidence-based theoretical models and up-to-date cognitive and behavioral principles for weight management. Furthermore, it targets overweight young adults with maladaptive eating habits that are at risk for obesity. Hence, the SIGMA intervention also incorporates attributes that are specific for preventive interventions and is, to our knowledge, the first evidence-based serious game for weight management. In addition, there are no RCTs that examined the efficacy of mHealth interventions in overweight and/or obese young adults, and even more so on individuals with maladaptive eating patterns.

Despite its advantages, the SIGMA intervention is subject to several limitations. Firstly, the data concerning maladaptive eating patterns, as well as weight and BMI, will be collected by means of self-report. Therefore, being susceptible to distortions resulting from social desirability effects. However, many of these outcomes require subjective judgments, thus self-reports are inevitable. When possible, we try to supplement our subjective measures with more objective ones, such as reaction times or daily step counts. Secondly, the decision to allow participants to follow a diet of their own choice potentially adds a source of variability in the results but only with regard to the secondary outcomes. However, as evidenced in a recent comprehensive meta-analysis, the ability to freely choose one’s diet promotes adherence to the weight-loss program [59]. Moreover, recent results indicate that different types of calorie-restrictive diets are equally effective as long as they are appropriately followed (e.g., [59, 60]). This approach is highly relevant for self-help programs enabling weight-loss monitoring in a self-guided matter. One example in this respect is the “Think Slim” intervention [61].

Overall, the SIGMA intervention has several noteworthy contributions, as exemplified in the following. *Firstly*, it relies on evidence-based practices for weight management in individuals challenged by maladaptive eating habits [36]. *Secondl*y, it not only addresses maladaptive eating patterns, such as emotional eating, food craving, binge eating, but it also addresses their cause as embodied by maladaptive cognitive styles. *Thirdly*, it aims at curbing the elevated attrition rates specific for weight management programs [62] by employing a gamified approach that is both interactive and engaging. *Fourthly*, SIGMA proposes an element of novelty among mHealth interventions for weight management in the sense that it includes cognitive techniques alongside standard behavioral techniques for long-lasting lifestyle changes and weight maintenance [7].

Given the increase in rates of obesity, we conclude that the SIGMA intervention may provide a cost-effective (i.e., always available) and preventive self-help tool for young overweight adults with maladaptive eating habits.

### Trial status

Recruiting
